### 3.2. Study Design

The research is organized into the following phases (Figure 1):

#### 3.2.1. Enrollment

The first phase requires two or three meetings. In the first meeting, the following data will be collected:(a)Personal demographics and clinical history;(b)Personal history: patient’s place and date of birth; details about both parents, whether they are alive or their age of death, cause of death, previous and/or current job, their number of siblings (including birth order), patient’s education; previous and current occupation; marital status and age when married; the age of their partner and his/her name, education, and occupation; their number of children, their names, ages, education level, and occupation; favorite personal hobbies; and any other relationships or information about their personal life that the patient feels is relevant to their health and well being.(c)Psychometric tests (see above);(d)The Six Drawing test (6DT).

All data will be kept in a dedicated folder and subsequently transferred to an electronic database.

In the following two encounters, the two qualitative questionnaires will be administered to all participants. Differences and peculiar characteristics, in particular, will be evaluated for in the psychometric tests, 6DT, and the two enrollment questionnaires.

#### 3.2.2. Treatment Choice, Implementation, and Group Allocation

In the second phase, all pts with TTS, AMI, and BC will be asked to freely choose between ontopsychological STP along with standard medical therapy and, whenever indicated, rehabilitation therapy or medical therapy plus rehabilitation alone.

Therefore, this phase results in seven study groups: three groups of pts (AMI, TTS, and BC) undergoing psychotherapy, three groups of pts (AMI, TTS, and BC) on standard medical therapy, and one group of HS.

There will be four independent areas of research: (1) AMI pts following psychotherapy (AMI-PSY) will be compared with AMI pts, without psychotherapy (AMI-C); (2) TTS pts who will follow psychotherapy (TTS-PSY) will be compared with TTS pts without psychotherapy (TTS-C); (3) BC pts with psychotherapy (BC-PSY), will be compared with BC pts without psychotherapy (BC-C); (4) HS subjects, after the initial comparative evaluation with the other enrolled groups, will have an independent follow-up, where psychological data collected at enrollment will be compared with psychological data collected at one year and with clinical follow-up at five years.

Since the research is observational, it is not possible to foretell how many patients will choose psychotherapy plus medical therapy or standard medical care alone.

If balanced patient groups can be formed, statistical analysis evaluating differences between groups will be performed. Thus, it may be possible to evaluate how psychotherapy may impact the real world because patients will have a choice between psychotherapy plus medical care or medical care alone. It will also be possible to evaluate if psychotherapy might result in an improvement in psychological patterns compared to medical therapy alone, and how this can translate in an improvement in medical prognosis. Moreover, the patients’ choice might provide useful information to improve a more individualized therapy and hospital organization.

AMI-PSY and TTS-PSY patients will be referred to the outpatient clinic of Cardiac Psychology at San Filippo Neri Hospital in Rome; BC-PSY will be referred to the outpatient clinic of Psycho Oncology in the same hospital. Psychotherapy will be provided in individual sessions (maximum of ten) and five group meetings, as in the STEP IN AMI trial. Psychotherapy will be conducted by two expert psychotherapists trained in ontopsychology and psychosomatics.

HS will not be offered psychotherapy but will be free to obtain private psychotherapy.

#### 3.2.3. Follow-Up

Follow-up is planned at one and five years with a comprehensive medical visit and yearly routine blood tests.

For AMI pts, echocardiography, an exercise stress test, or stress myocardial perfusion scintigraphy, will be performed when medically indicated.

For TTS pts echocardiography is timetabled at one month and six months after the acute phase, and yearly through the five-year follow-up when indicated.

For BC pts, history, physical examination, and mammography will be obtained at follow-up. Physical examination is planned every 3 to 6 months for the initial 3 years, every 6 to 12 months for years 4 and 5, and annually thereafter. For women who have undergone breast-conserving surgery, a post-treatment mammogram is scheduled 1 year after the initial mammogram and at least 6 months after completion of radiation therapy. Thereafter, unless otherwise indicated, a yearly mammogram will be scheduled. The use of complete blood counts, chemistry panels, bone scans, chest radiographs, liver and pelvic ultrasound, computed tomography scans, fluorodeoxyglucose–positron emission tomography scans, magnetic resonance imaging, and/or tumor markers (carcinoembryonic antigen, CA 15-3, and CA 27.29) are not recommended for routine follow-up in an otherwise asymptomatic patient with no specific findings on clinical examination [56].

At the one-year follow-up all patients and HS will be administered: (a) the same psychometric tests administered at enrollment; (b) two qualitative questionnaires, the 1-year follow-up body perception questionnaire (Supplementary Material S2), and the 1-year follow-up dream questionnaire (Supplementary Material S4); (c) the 6DT.

At the five-year follow-up, all psychometric tests will be administered to all of the groups.

Data will be recorded on paper case-report forms and transferred into an electronic database, with the principal investigator cross-checking consistency of data for all patients.

## 4. Statistical Analysis

An external committee will evaluate the results in each phase of the research and the characteristics of each group will be analyzed. The qualitative results related to the 6DT, body perception questionnaire, and dream questionnaire at enrollment and the one-year follow-up. It is impossible to foretell the specific features of oneiric symbols and patterns before the study, as the research is a pilot study in the field of psychosomatics. The oneiric manual of the ontopsychological school [45] will be used as an initial reference point for the analysis and classification of dreams.

Unless otherwise specified, all study data will be analyzed on an intention-to-treat basis.

Event rates will be expressed as proportional incidences and as person−time incidence rates. Continuous variables for each of the study groups will be reported as means (with standard deviations or 95% confidence intervals) or as medians (lower quartile-upper quartile), as appropriate; categorical variables will be reported as absolute numbers and percentages. Continuous unpaired variables will be compared using the independent-sample Student’s t or Mann-Whitney U tests, and continuous paired variables will be compared using paired Student’s t or Wilcoxon tests, as appropriate. Categorical variables will be compared by Pearson’s chi-squared analysis or Fisher’s exact test, as indicated. The outcome incidence within each study group over long-term follow-up will be compared with Friedman’s test. Survival analysis will be performed using Cox proportional hazards ratios. Multivariable binary logistic regression analysis will be performed to appraise the independent predictive role of baseline characteristics on outcomes. Spearman’s rank correlation test will be performed to assess the correlation between variables. A *p* value < 0.05 will be considered statistically significant, with all inferential tests 2-tailed. Statistical analysis will be performed using the statistical software program SPSS, version 11.5 (SPSS Inc., Chicago, IL, USA).

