## Abstract

Psychosocial factors play an important role in non-communicable diseases (NCDs). This observational study is primarily aimed at assessing the relationship of psychological characteristics of patients with the outcomes of different NCDs, and to assess short-term psychotherapy (STP) efficacy in the real world. **Methods**: One hundred and forty patients with recent acute myocardial infarction, Takotsubo syndrome, or non-metastatic breast cancer and a control group of 140 age and sex-matched healthy subjects, will be enrolled. All subjects will be administered psychometric tests, quality of life tests, a specific body perception questionnaire, a dream questionnaire, and a projective test, the Six Drawing test at baseline and follow-up. All subjects with medical conditions will be asked to freely choose between an ontopsychological STP along with standard medical therapy and, whenever indicated, rehabilitation therapy or medical therapy plus rehabilitation alone. The study endpoints will be to evaluate: the relationship of the psychological characteristics of enrolled subjects with the outcomes of different NCDs, predictors of the choice of psychotherapy, and the efficacy of ontopsychological intervention on psychological and medical outcomes. **Conclusion**: This study will generate data on distinctive psychological characteristics of patients suffering from different CDs and their relationship with medical outcomes, as well as explore the efficacy of ontopsychological STP in these patients in the real world. (Number of registration: NCT03437642).

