### 3.1. Tests

The following psychometric tests, previously used in the STEP IN AMI trial, will be administered to all subjects in all four groups at enrollment and at the one and five-year follow-up: the Self-evaluation test, assessing the global level of psychological distress over the preceding two weeks [46]; the Social Support Questionnaire, evaluating the individual’s perception of his/her social network [47,48]; and the Beck Depression Inventory (BDI), evaluating symptoms of major or minor depression [30,31], where a score between 10 and 15 is considered indicative of mild depression symptoms, and a score equal or higher than 16 indicates clinically significant depression. In addition, the State-Trait Anxiety Inventory (STAI) [49] and State-Trait Anger Expression Inventory (STAXI 2) [50] will also be administered at the same time points.

Quality of life will be evaluated at enrollment and after one and five years in AMI, TTS, BC patients, and HS. In patients with AMI and TTS, the Mac New Heart Disease Health-Related Quality of Life Questionnaire will be utilized to assess three specific domains: emotional, physical, and social, as well as a global QOL score [33].

In women with BC two specific psychometric tests evaluating quality of life have been selected: the EORTC QLQ-C30 (European Organization for Research and Treatment of Cancer Quality of Life- Cancer 30, version 3) [51] and the QLQ-BR23 (Quality of Life Questionnaire for Breast cancer 23) as a supplement for assessing specific quality of life issues relevant to patients with breast cancer [52]. The QLQ-C30 incorporates nine multi-item scales: five functional scales (physical, role, cognitive, emotional, and social); three symptom scales (fatigue, pain, nausea, and vomiting); and a global health and quality of life scale. The QLQ-BR23 consists of 23 items covering symptoms and side effects related to different treatment modalities, body image, sexuality, and future perspective.

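### For continuous scores the plan states no between-group analysis that accounts for baseline, although patients choose psychotherapy themselves and every score is taken at enrolment

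*Protocol article*

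**What the plan says.** All references are to the protocol article.

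- **Allocation** (3.2.2): "all pts with TTS, AMI, and BC will be asked to freely choose between ontopsychological STP along with standard medical therapy". The groups are self-selected.
- **Aim**: the Abstract lists as an endpoint "the efficacy of ontopsychological intervention on psychological and medical outcomes". Section 3.2.2 adds: "It will also be possible to evaluate if psychotherapy might result in an improvement in psychological patterns compared to medical therapy alone". It sets the comparison of patients with and without psychotherapy separately within each of the three diseases.
- **Data** (3.1): the psychometric tests "will be administered to all subjects in all four groups at enrollment and at the one and five-year follow-up". Quality of life follows the same visits, with a cardiac instrument for infarction and Takotsubo patients and two cancer instruments for breast cancer patients.
- **Tests for continuous variables** (4): for separate groups, "Continuous unpaired variables will be compared using the independent-sample Student’s t or Mann-Whitney U tests". For repeated measurements in the same subjects the rule is: "continuous paired variables will be compared using paired Student’s t or Wilcoxon tests, as appropriate".
- **Regression models** (4): Cox regression for event times, and: "Multivariable binary logistic regression analysis will be performed to appraise the independent predictive role of baseline characteristics on outcomes".
- **Significance** (4): a p "value < 0.05 will be considered statistically significant, with all inferential tests 2-tailed".

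**The concern.** Distress plausibly drives the choice of psychotherapy, and distress is what these scores measure. The Abstract itself names predictors of that choice as an endpoint, so the study expects that choosers and decliners may differ at enrolment.

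If they do, a two-sample test on follow-up scores carries part of the initial gap forward. A two-sample test on change credits the group that started worse with its regression to the mean. Paired tests within each group never compare the two groups. The two regression models named do not fill the hole, because one is for event times and the other for binary outcomes.

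At stake is the psychological efficacy claim in each disease, which could be wrong in either direction although the baseline scores that would help are already in the database.

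**Working it through.** **The plan's own figure.** No sample size or effect size is stated for any score. The one sizing figure, 55 infarction patients, rests on a binary composite of 43% against 78%. The unpooled formula (1.960 + 0.842)² × (0.43×0.57 + 0.78×0.22) / 0.35² gives 26.7 per arm, or 54 in total, close to 55. It does not bear on the scores. It is used here only for an even split of 28 against 27.

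**Assumptions (none is in the documents).** Baseline and follow-up scores have SD 1 and correlation r of 0.5–0.7. Choosers start g SD worse. Therapy has no effect. The expected gap at follow-up is r × g.

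**Formulas.** The standard error factor is √(1/28 + 1/27) = 0.2697, with 53 degrees of freedom and rejection rates from the non-central t.
- Follow-up test: expected difference r × g, SD 1.
- Change test: expected difference −(1 − r) × g, SD √(2(1 − r)).

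**Results at g = 0.5**

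| r | Follow-up bias | Non-centrality | Rejects | Change bias | SD of change | Non-centrality | Rejects |
|---|---|---|---|---|---|---|---|
| 0.5 | 0.25 | 0.927 | 14.9% | 0.25 | 1.000 | 0.927 | 14.9% |
| 0.6 | 0.30 | 1.112 | 19.4% | 0.20 | 0.894 | 0.829 | 12.9% |
| 0.7 | 0.35 | 1.298 | 24.7% | 0.15 | 0.775 | 0.718 | 10.9% |

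**Direction.** At r = 0.6 the follow-up test's 19.4% splits into 19.3% apparent harm and 0.1% apparent benefit. The change test's 12.9% splits into 12.6% false benefit and 0.3% the other way. If choosers start better, both directions reverse.

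**Other gaps.** At g = 0.3 the follow-up test rejects in 8–12% and the change test in 7–8%. At g = 0.8 the ranges are 31–53% and 20–31%. With no gap both hold about 5%.

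**Uneven splits.** Choices so far are 15:4 in Takotsubo, 5:6 in breast cancer and 1:3 in infarction. Scaled to the planned sizes, 30 × 15/19 ≈ 24 against 6, and 55 × 1/4 ≈ 14 against 41. At g = 0.5 the follow-up test rejects in 8–11% (24 v 6) and 12–20% (14 v 41), and the change test in 7–8% and 9–12%. The bias in SD units is unchanged. The lower rates only reflect lower power.

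**Separate paired tests.** In simulation with 28 v 27 and g = 0.5, a significant improvement appeared in the therapy group alone in 16–23% of runs, with no therapy effect.

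**Baseline-adjusted regression (ANCOVA).** Under the same assumptions, simulation gave an adjusted difference of about 0 and 4.2–5.6% rejections in every scenario.

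**If the gap is stable instead.** Let choosers differ by a persistent trait, so that the gap stays at g. ANCOVA is then off by (1 − r) × g. At r = 0.6 that is 0.4 × 0.5 = 0.20 SD, with about 14–15% rejections, or 0.4 × 0.8 = 0.32 SD, with about 27%. The change score then holds 5%.

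**The case against.** **The list in section 4 is generic.** It ties no test to a score, visit or contrast. A reader might infer that the plan compares follow-up scores alone and ignores baseline. The text does not say so: a two-sample test on change fits the wording equally well, and the paired tests use baseline within a group. Nor does it propose to infer efficacy from significance in one group but not in the other. This stands, so the point is limited to the absence of a stated group comparison that accounts for baseline.

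**The error need not favour therapy.** A reader might infer that regression to the mean will pass as a therapy effect. That holds only for change or paired analyses when choosers start worse. A follow-up test then errs against therapy.

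**ANCOVA is no sure cure.** With self-selected groups and instruments that partly measure traits, the gap may persist, and ANCOVA is then the biased method. The documents do not say which case holds. This stands and shapes the fix.

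**Testing is conditional and partly exploratory.** Section 3.2.2 makes group comparisons depend on forming balanced groups, and the Takotsubo and breast cancer comparisons are called exploratory. But balance is not defined, section 3 speaks only of sufficient group size, and equal numbers do not give equal baseline scores.

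**An article leaves detail to a fuller plan.** True of covariate lists. Here, however, the article names its tests one by one, down to the software version, and those it names do not suit self-selected groups. The logistic model could be run on a dichotomised depression score, but the text does not say so and it would not serve the continuous scales.

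**Conclusion.** The point holds in a limited form. For continuous scores the article states only unadjusted two-sample tests and within-group paired tests, and neither compares choosers with decliners at equal baseline. With a 0.5 SD gap and no therapy effect, the nominal 5% error becomes about 15–25% for a follow-up test (apparent harm) or 11–15% for a change test (false benefit).

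These sizes rest on an assumed gap, direction, correlation and near-even split, and on a gap that shrinks with the correlation. None is documented, and with no gap there is no inflation. The documents do not support the claim that the plan will produce a false therapy benefit, nor that baseline adjustment would make the comparison unbiased. They do support saying that an adjustment available from data already collected is not part of the stated analysis. It should be changed, but it is not fatal to the study.

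**What to change.** Within each disease separately, regress the follow-up score on treatment choice with the baseline score as covariate. Add age, and sex where it varies, as group size allows. Diagnosis is constant in these comparisons, and sex is constant in breast cancer. Report the adjusted difference with its 95% CI.

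Prespecify a change-score analysis as sensitivity, because it is the unbiased one if the baseline gap is a stable trait. A conclusion that holds under both is more secure, and one that does not should be reported as unresolved. Keep paired tests as description within groups, not as evidence of efficacy. State that confounding by choice remains after adjustment.

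No new data are needed. The cost is a little more analysis and wording, and possibly a less favourable or less clear result.

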### 2.2. Participants

#### 2.2.1. Inclusion Criteria

(1)Patients with AMI with ST-elevation on the admission electrocardiogram (STEMI) and without ST elevation (NSTEMI) treated with urgent percutaneous coronary intervention (PCI); up to 12 h for STEMI and 48 h for NSTEMI patients.

According to the Fourth Universal Definition of Myocardial Infarction, acute myocardial injury is defined as the presence of either positive troponins with a rise-and-fall pattern, a fall-only pattern (in case the first available troponin was the peak), or a rise-only pattern [35,36].

(2)Patients with TTS

Diagnosis of TTS is based on the modified Mayo Clinic Diagnostic Criteria including (1) transient wall motion abnormality of the left ventricle with extension beyond a single epicardial coronary artery distribution; (2) absence of obstructive coronary artery disease or angiographic evidence of acute plaque rupture; (3) new electrocardiographic abnormalities or troponin value increase; and 4) the absence of myocarditis or pheochromocytoma at index hospitalization [12,37,38].

Although TTS was initially described with angiographically normal coronary arteries, smaller studies recently indicated a potential coexistence of coronary artery disease (CAD) in TTS patients [39]. To avoid confusion in the initial diagnosis, in this protocol TTS pts without critical coronary artery stenosis will be enrolled.

(3)Patients recently operated on for non-metastatic BC treated with radiotherapy and/or chemotherapy and/or hormone therapy.(4)A control group of subjects without major active diseases (HS), matched for age and sex. This includes subjects without clinical evidence of major diseases that required hospitalization in the last ten years or chronic medical therapy (e.g., anti-neoplastic, immunosuppressant, cortisone, psychiatric, etc.), and not undergoing or scheduled for psychotherapy at enrollment.

Inclusion criteria for all patient groups include an age between 30 and 75 years old, the ability to provide written informed consent to participate in the study, and availability to undergo psychotherapeutic treatment.

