##### Sample Sizing

The size of the AMI group has been based on evaluation of the outcome data at one year from the results of the STEP-IN-AMI trial: a 43% incidence of the primary composite endpoint is expected in the psychotherapy group and 78% in the control group; therefore, 55 pts will be enrolled to achieve statistical power at the 95% confidence level with 80% power. Given the exploratory nature of the study in the other groups, which renders impossible any hypothesis on the effects of psychotherapy, statistical sample sizing has not been performed in these groups. To match the AMI group, 55 women with BC will also be enrolled. However, only 30 patients with TTS will be enrolled for feasibility reasons, due to the lower percentage of patients admitted to the hospital as compared to the other study groups which could unreasonably slow the enrollment phase. Consequently, it will be necessary to enroll 140 HS in the control group.

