### Enrollment Status

At this time, 75 out of a total of 280 subjects have been enrolled: 19 with TTS (15 have chosen psychotherapy); 11 women with BC (5 have chosen psychotherapy); 4 with AMI (1 has chosen psychotherapy); 41 HS.

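### Student's t is named for unpaired scores although 30 or 55 patients may face 140 healthy subjects; Welch's t would protect the error rate if the spreads differ

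*Protocol article*

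**What the plan says.** **Test.** Section 4 of the protocol article states "Continuous unpaired variables will be compared using the independent-sample Student’s t or Mann-Whitney U tests", and goes on "continuous paired variables will be compared using paired Student’s t or Wilcoxon tests, as appropriate". It does not mention equal or unequal variances. The significance rule is a p "value < 0.05 will be considered statistically significant, with all inferential tests 2-tailed".

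**Group sizes.** Under Sample Sizing, "55 pts will be enrolled to achieve statistical power at the 95% confidence level with 80% power" (the AMI group), then "To match the AMI group, 55 women with BC will also be enrolled". TTS is limited to 30 for feasibility. The section concludes: "Consequently, it will be necessary to enroll 140 HS in the control group".

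**Who the HS are.** Section 2.2.1 defines them as "subjects without clinical evidence of major diseases that required hospitalization in the last ten years or chronic medical therapy", with psychiatric drugs among its examples of such therapy. They must also be neither in psychotherapy nor scheduled for it, and they are matched for age and sex. Patients face no comparable screen: section 2.2.2 lists no psychiatric exclusion, and section 2.3 records psychopharmacological treatment without excluding it.

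**What is compared.** Sections 3 and 3.1 give the distress, social support, depression, anxiety and anger scales to all four groups. Section 3.2.1 says that differences will be looked for in the psychometric tests. Section 3.2.2 treats HS as one group that is first compared with the other enrolled groups.

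**The concern.** The pooled standard error weights each group's variance by its degrees of freedom, so it is governed mainly by the larger group. If the smaller group is the more variable one, the standard error comes out too small and the test rejects too often. In the reverse case it rejects too rarely.

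The design makes the first case plausible. The larger group is the one screened for health and therapy, which could remove some high distress scores, while the smaller groups are not screened in that way. A patient group that differed from HS only in spread could then be reported as differing in mean more often than the 5% the plan intends. These comparisons serve the aim of describing what sets each patient group apart psychologically.

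**Working it through.** **Inputs.** The group sizes come from Sample Sizing. The plan's 140 reproduces exactly: 55 + 55 + 30 = 140, one HS per patient. The level is two-sided 0.05, from section 4. The article gives no SDs, so the ratio r = patient SD / HS SD is an assumption, taken as 1.0, 1.1, 1.25, 1.5 and 2.0 with the HS SD set to 1.

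**Formulas**, with n₁ patients and n₂ HS:
- Pooled variance: s² = [(n₁ − 1)r² + (n₂ − 1)] / (n₁ + n₂ − 2)
- Standard error used by Student's t: √[s²(1/n₁ + 1/n₂)]
- True standard error: √(r²/n₁ + 1/n₂)
- Approximate true error: 2[1 − Φ(1.96 × SE used / SE true)]

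**30 v 140, r = 1.5**
- s² = (29 × 2.25 + 139)/168 = 1.216
- SE used = √[1.216 × (1/30 + 1/140)] = 0.222
- SE true = √(2.25/30 + 1/140) = 0.287
- SE true / SE used = 1.292
- Error ≈ 2[1 − Φ(1.96/1.292)] = 0.129

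**55 v 140, r = 1.5**
- s² = (54 × 2.25 + 139)/193 = 1.350
- SE used = √[1.350 × (1/55 + 1/140)] = 0.185
- SE true = √(2.25/55 + 1/140) = 0.219
- SE true / SE used = 1.186
- Error ≈ 2[1 − Φ(1.96/1.186)] = 0.098

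**Simulation** with equal means and normal data (60,000 replicates for the t tests, 20,000 for Mann-Whitney). Entries are the percentage rejected at nominal 5%:

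| Groups | r | Student | Welch | Mann-Whitney |
|---|---|---|---|---|
| 30 v 140 | 1.0 | 5.0 | 5.1 | 4.9 |
| 30 v 140 | 1.1 | 6.3 | 4.9 | 5.4 |
| 30 v 140 | 1.25 | 8.8 | 5.0 | 6.7 |
| 30 v 140 | 1.5 | 12.8 | 5.0 | 8.4 |
| 30 v 140 | 2.0 | 19.3 | 4.9 | 11.1 |
| 55 v 140 | 1.0 | 4.9 | 4.9 | 5.0 |
| 55 v 140 | 1.1 | 5.8 | 4.9 | 5.5 |
| 55 v 140 | 1.25 | 7.6 | 5.1 | 6.6 |
| 55 v 140 | 1.5 | 9.7 | 5.1 | 7.4 |
| 55 v 140 | 2.0 | 13.4 | 4.9 | 9.3 |

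**Size-matched comparison.** With n₁ = n₂ = n, both standard errors equal √[(r² + 1)/n], so the distortion cancels. In simulation, Student's t at 30 v 30 and 55 v 55 stayed between 4.9% and 5.3% for every r up to 2.

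**Skewed scores** (gamma, equal means, r = 1.25, 1.5, 2.0):
- 30 v 140: Student 8.9%, 12.7%, 19.8%; Welch 6.4%, 7.0%, 8.6%
- 55 v 140: Student 7.4%, 9.8%, 14.1%; Welch 5.4%, 5.9%, 7.1%

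**The case against.** **The comparator is not stated.** The 140 is one HS per patient and HS are matched for age and sex, so each patient group might be set against its own controls, where nothing is inflated. This stands as a condition on the finding. The text leans the other way: it speaks of one HS group throughout, never divides it by disease, and does not tie the paired tests to the matching.

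**Student's t is not mandatory.** The sentence leaves the choice between the t test and Mann-Whitney open. That is true, but on normal data Mann-Whitney also exceeds 5% under unequal spread: 8.4–11.1% at 30 v 140 for r of 1.5 to 2. The open choice softens the problem without removing it.

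**The SDs are unknown.** A reader might infer that false differences will be two to four times too frequent. The documents do not support that as a flat statement. It needs r of 1.5 to 2 and all 140 HS as comparator. Nearly four times (19.3/5) arises only for TTS at r = 2; the groups of 55 reach at most 2.7 times (13.4/5). At r = 1.25 the factor is 1.5 to 1.8, and at r = 1.1 about 1.2 to 1.3.

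**Screening may lower the HS mean too.** Removing high scores would shift the mean as well as the SD, so exactly equal means may not hold. This is fair. The same standard error would still be too small for any interval around the difference: at 30 v 140 and r = 1.5, a nominal 95% interval would cover about 100 − 12.8 = 87%.

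**The psychotherapy contrast.** A reader might extend the point to TTS with and without psychotherapy. Recruitment stands at "19 with TTS (15 have chosen psychotherapy", that is 15 v 4, and 30 × 15/19 ≈ 24 projects to 24 v 6. Section 3.2.2 makes those tests conditional on balanced groups, so the contrast is not part of this finding.

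**Article-level detail and an exploratory aim.** How a t test treats variances is often left to a fuller document, and the Discussion describes the main purpose as qualitative. This keeps the point minor. The article does, however, name a specific test that suits these group sizes poorly.

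**Conclusion.** The point holds as a minor, conditional one. Student's t is the named parametric test, and the planned sizes are 30, 55 and 55 against 140. If all 140 HS are the comparator and the patient SD is 1.25, 1.5 or 2.0 times the HS SD, the true error on normal data is about 9%, 13% and 19% for TTS, and 8%, 10% and 13% for AMI or BC. There is no inflation if the SDs are equal or the comparison is size-matched. If patients were the less variable group, the test would be too conservative instead.

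The documents show neither that the spreads differ nor by how much. They show only that the screening makes a narrower HS spread plausible. The case for changing the test is that protection costs almost nothing, not that inflation has been demonstrated.

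**What to change.** In section 4, replace the independent-sample Student's t test by Welch's unequal-variance t test for unpaired comparisons of continuous variables. This changes one phrase, needs no new data, and loses only a trivial amount of power if the SDs turn out equal. Welch's test is not exact for skewed scores at these sizes (roughly 6–9% at 30 v 140), but in every unequal-spread setting examined it was closer to 5% than Student's t.

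Two additions are optional. One is a sentence saying whether each patient group is compared with all HS or with its own matched controls, which would settle the main condition above. The other is a rank test that allows unequal spread, such as Brunner-Munzel, wherever a rank test is preferred.
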